**Figure 1 FIG1:**
[figure not shown]
Intervention study process flow ARPE: Augmented Reality Physical Ergonomics; DOSH: Department of Occupational Safety and Health

Introduction phase (t0): The intervention group will receive a briefing on AR physical ergonomic training and download the MAKAR XR app, which includes instructions to familiarize them with its interface and tasks. The control group will undergo traditional ergonomic training, which will begin with a briefing and lectures based on the DOSH MMH guidelines [25]. This training will focus on preventing ergonomic injuries and MSDs, emphasizing the importance of taking breaks, using adjustable tools, proper lifting techniques, maintaining good posture, and conducting posture assessments. It will cover reporting WMSD symptoms, consulting healthcare providers, and ergonomic hazard management, promoting safe task performance, and adherence to health guidelines. Self-evaluation will assess MMH techniques, WMSD risk factors, potential hazards, and control initiatives such as stretching. This session will last 30-45 minutes and will include baseline assessments on knowledge, self-prevention, and self-evaluation for both groups.

Intervention phase (t1): This phase assesses knowledge acquisition and retention through questionnaires. Participants receive WhatsApp reminders to engage with AR content in the MAKAR XR apps and adhere to the MMH guidelines. They should view the ARPE module training within two to three days and can provide feedback to the researcher via WhatsApp. Regular WhatsApp check-ins and automated reminders will track participant engagement and potential dropouts. Weekly or bi-weekly check-ins will be conducted to inquire about participants' progress and address any issues. Missing multiple reminders will prompt additional follow-up to address the potential problems with dropouts.

Post-intervention phase (t2): In the sixth week, a follow-up and post-evaluation of the training will occur. Post-evaluation on the domains of self-prevention and self-evaluation will be assessed by disseminating questionnaires to the participants. This phase aims to measure the long-term retention of ergonomic knowledge and the practical application of self-prevention and self-evaluation techniques learned during the training. Data collected will be analyzed to determine the effectiveness of the AR training module compared to the conventional training method.

Quality control measures will be implemented to minimize study contamination, with participants instructed not to share the messages they received. Recruitment efforts ensure that participants from both the intervention and control groups are drawn from distinct warehouse locations. Recruitment focuses on workers who willingly agree to commit to the study, aiming to enhance compliance with the intervention. Participants are advised to adhere strictly to the intervention procedure, which involves actively observing and comprehending each aspect of the ARPE training intervention throughout the designated study period. To ensure compliance with the protocol, participants will be instructed not to share details of the intervention and must follow the ARPE training guidelines. Adherence will be monitored through regular WhatsApp check-ins and confirmation from supervisors. Supervisors will be asked to verify their employees' participation, emphasizing the importance of the intervention and fostering a supportive work environment. Instances of non-compliance, such as missed sessions, will lead the researcher to reach out, offering assistance and encouraging continued participation, thereby supporting the successful implementation of the intervention. This strategy is anticipated to greatly enhance the overall effectiveness of the study by keeping participants engaged and compliant with the training protocols. Participants received weekly reminders, and adherence was monitored through supervisor sign-offs and app analytics. Outcome assessors and analysts remained blinded to allocation.

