## Results

Planned outcomes and data analysis

Since this is a protocol, no results are available yet. The primary outcome is ergonomic knowledge, while secondary outcomes include self-prevention behaviors and self-evaluation, measured at baseline (T0), post-training (T1), and six weeks later (T2). Analyses will follow intention-to-treat principles using repeated-measures mixed models (fixed effects: group, time, group×time), with site effects and adjustments for baseline scores and prespecified covariates (e.g., age, tenure, department/shift, prior training). Two-sided α=0.05; results will be reported as adjusted mean differences with 95% CI. Sensitivity analyses will incorporate site-clustered standard errors (SEs), a random intercept for the site if applicable, and inverse-probability-of-treatment weighting. Outcome assessors and the statistician will remain blinded to group allocation. 

Protocol Status and Timeline

Recruitment and baseline assessments are ongoing; follow-up continues through November 2025, after which data will be cleaned and analyzed. No interim results are available.

Interpretation of Change

A structured outcome framework was created to assess the effectiveness of the ARPE training module. The assessments are divided into three domains: ergonomic knowledge (the primary outcome), self-prevention behaviors (secondary outcome 1), and self-evaluation skills (secondary outcome 2). Each domain is evaluated at three key timepoints: baseline (t_0_, before the intervention), week 1 (t1, after the intervention to assess knowledge), and week 6 (t2, follow-up post-intervention). The tools used are adapted from Diego-Mas et al. [14]. All scales are scored so that higher scores reflect better outcomes. The primary endpoint is the change in ergonomic knowledge from baseline to immediate post-training (T0→T1). ARPE will be considered superior if the adjusted group-time effect (ARPE-control) is positive with a 95% CI that does not include 0 (two-sided α=0.05); persistence will be evaluated at T2. For secondary domains (self-prevention, self-evaluation), adjusted group×time effects at T1 and T2 will be regarded as improvements when the 95% CI excludes 0; these analyses are exploratory and supportive.

Baseline Characteristics

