Baseline data collection will occur during the participants' first training session, before their enrolment in the study. Both primary and secondary outcomes will be evaluated at three intervals: the baseline measurement, the end of the first week, and the conclusion of the sixth week. Participants will receive prompts to complete data collection at each point through direct reminders and easy survey submission options. During baseline collection, reminders will be provided at the initial training session, with notifications sent via WhatsApp or phone calls, as preferred by the participants. During recruitment, participants will fill out self-administered questionnaires using a Google Form. For follow-up assessments in the first and sixth weeks, the same communication channels will be used for reminders, and the Google Form will be the sole method for these evaluations. These reminders will be strategically timed to foster consistent engagement and compliance, thus facilitating accurate data collection throughout the study. This strategy ensures a thorough, flexible, and efficient monitoring of data collection over the two months.

Data Management

In the data management domain, we are committed to upholding the privacy and confidentiality of participants. To achieve this, each participant will be assigned a unique anonymous research identification number (ID). Participant names and data will be securely stored on a password-protected researcher's laptop, linked exclusively to their respective research ID for this study. Regular data backups will be executed and stored in a secure location. Upon the study's conclusion, data on the computer will be transferred to an external hard drive, and the computer data will be permanently erased. Both external hard drives and hardcopy data will be safeguarded in a locked office designated for researchers. The data will be retained for at least three years post-study completion, after which it will be systematically erased. This stringent data management protocol ensures the highest data security and participant confidentiality throughout and beyond the study period.

Data Analysis

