## Discussion

This protocol evaluates whether an AR-based physical ergonomics module (ARPE) improves ergonomic knowledge (primary) and self-prevention/self-evaluation (secondary) among MMH workers compared to guideline-based training. AR addresses the limitations of passive formats by increasing engagement, interactivity, and task-specific feedback, which are linked to better learning and skill transfer in professional training [26,27]. The quasi-experimental site/shift-level design aims to minimize cross-group contamination while allowing evaluation under routine working conditions [28]. Conventional classes and videos often fall short in changing behavior during high-risk tasks [7,11]. By incorporating 3D simulations and in situ cues, ARPE is expected to support deeper encoding, immediate feedback, and context-specific practice, potentially leading to safer work techniques. This study extends AR/VR training evidence to warehouse MMH ergonomics using validated tools, a prespecified analysis plan, and blinded assessment/analysis, which improves interpretability [26,27]. Strengths include alignment with occupational guidance and measures validated locally, pragmatic site/shift assignment to minimize contamination, repeated measures at T0, T1, and T2 to evaluate immediate gains and short-term durability, and a pre-planned model of group×time effects with covariate adjustment and site effects. Limitations persist. Additionally, we will perform inverse-probability-weighted sensitivity analyses. Self-report outcomes may be influenced by social desirability bias [29]; mitigation strategies include the use of anonymous, self-administered tools, blinded assessors and analysts, and aggregate reporting. Non-randomized allocation could lead to selection bias and site-level confounding [30]. We will report baseline comparability using SMDs, adjust for age, tenure, department/shift, and prior training, and include site effects. Contamination will be minimized through separate sites/shifts, instructions not to share materials, and routine schedule reminders. Expected attrition and varying digital literacy are addressed through weekly reminders, supervisor sign-offs, app usage analytics, and an intention-to-treat analysis with proper handling of missing data (MAR/MCAR). Residual confounding remains possible and will be considered in cautious interpretation.

Implications and future directions

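### Outcome assessment is described as blinded and the tools as anonymous, but unblinded workers complete every outcome themselves under name-linked IDs, so neither claim can count as mitigation of social desirability bias

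*Protocol article*

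**What the plan says.** The blinding claim appears in three places in the protocol article. The quality-control paragraph under Intervention states "Outcome assessors and analysts remained blinded to allocation". Results, Planned outcomes and data analysis, repeats it: "Outcome assessors and the statistician will remain blinded to group allocation". The Discussion then relies on it twice. It counts blinded assessment and analysis as an aid to interpretability. After conceding that "Self-report outcomes may be influenced by social desirability bias", it adds that "mitigation strategies include the use of anonymous, self-administered tools, blinded assessors and analysts, and aggregate reporting".

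On how outcomes are collected, Data Collection says that during recruitment "participants will fill out self-administered questionnaires using a Google Form", and for weeks 1 and 6 that "the Google Form will be the sole method for these evaluations". On what participants know, the introduction phase under Intervention says "The intervention group will receive a briefing on AR physical ergonomic training and download the MAKAR XR app", while the control group has a briefing and lectures based on the DOSH guidelines. On identity, Data Management says that names and data are "linked exclusively to their respective research ID for this study", and the ethics section describes coded IDs with identifiers held separately.

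**The concern.** Blinding an outcome assessor protects a result when someone other than the participant makes the judgement. Where participants rate themselves, only blinding the participants would do this, and here the two trainings are openly different. The article acknowledges the right bias but says it is handled partly by measures that are absent (a blinded assessor, anonymity) or that act elsewhere (a blinded analyst).

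The secondary outcomes are at stake. Self-prevention and self-evaluation are means of 7-point Likert self-ratings. The self-evaluation score draws on the RQ, which covers prior AR exposure, expectation, interest and usefulness, so answers may well depend on knowing one's arm. Under Interpretation of Change, a secondary effect is regarded as an improvement once its 95% CI excludes zero, and the section on implications links supportive behaviour change to scaling up. A reader told that assessment was blinded and anonymous would give such a result more weight than it can bear.

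**Working it through.** The documents contain no figure for this point, so the check sets the statements side by side.

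1. **Who assesses the outcome?** Primary and secondary outcomes are measured at baseline, week 1 and week 6. Baseline is self-administered, and at both follow-ups the Google Form is the only route. No rater, interviewer or observer is described for any outcome. The assessor is the worker.

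2. **Does the assessor know the arm?** One arm is briefed on AR and installs the app; the other attends lectures. The worker knows which training was received. From steps 1 and 2, the blinded-assessor statement has nothing to refer to for these outcomes.

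3. **Are the tools anonymous?** Each worker has a research ID linked to a name, and three repeated measures per person have to be joined. Responses are coded and can be traced by the research team, so they are confidential rather than anonymous. This matters because anonymity is offered as a reason for workers to answer frankly.

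4. **Is analyst blinding contradicted?** No. It is fragile, for three reasons:
   - Under Allocation, each arm is one warehouse, and the article says which of the two is the intervention site.
   - The models in the outcome sections and in Data Analysis contain both group and site. With 2 sites × 39 workers × 3 visits = 234 rows, a design matrix holding an intercept, group, two time terms, two group×time terms and site has 7 columns and rank 6. Site and group are the same variable, so anyone who recognises the site knows the arm. (What this does to the model itself is a separate matter.)
   - The adherence text mentions app analytics, which would concern the ARPE app. If passed to the analyst, they would reveal the arm.

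5. **Would analyst blinding help with this bias?** No. Social desirability acts when the worker answers, before any analyst sees the data.

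6. **What remains of the mitigation list?** Self-administration is real and removes interviewer influence. Aggregate reporting is real and is also stated in the ethics section. Blinded assessors and anonymity fall away. Blinded analysts may exist, but do not act on this bias.

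**The case against.** The strongest defence has four parts.

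- **Analyst blinding.** A reader might infer that the design has no blinding at all and that the statistician cannot be blinded. The documents do not support that. They state that the statistician is blinded, nothing prevents work on neutral group and site labels, and nothing says app-use data reach the analyst. The masking mechanism may properly sit in a fuller document. This part stands.

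- **Anonymity.** *Anonymous* may be loose wording for coded. Data Management itself calls the ID anonymous while linking it to names. A reader might also infer that supervisors see answers. The text only has them verify participation. This part stands as to supervisors. The wording still needs correcting, because it is used as a bias safeguard.

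- **Existing caution.** The article names social desirability as a limitation, labels the secondary analyses exploratory, and calls for objective task measures in future. That softens the harm but does not cure it, since the limitation is presented as mitigated.

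- **Size of harm.** Superiority rests on knowledge, described under Assessment Tool Development and Validation as a test scored 0-100%. A scored test is less open to reporting bias than Likert ratings, although Table 1 lists the PQ questionnaire for it. Both arms also know they are being trained, and inflation common to both cancels in the group×time contrast; only a differential shift would bias it. A reader might infer that a favourable ARPE difference would simply be reporting bias. That is not shown, and the documents give no input from which to estimate such a shift.

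**Conclusion.** The point holds in a limited form. The blinded-assessor claim is contradicted by the article's own data collection, and the anonymity claim by its own data management. Analyst blinding is not contradicted; it is fragile, and irrelevant to the bias it is cited against.

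No numerical size can be given from the documents. The reach is clear: all three outcomes are self-completed, and the exposure is greatest for the two Likert secondary outcomes at week 1 and week 6. The conclusion assumes only that no outcome has an assessor other than the worker, and none is described. It does not assume that bias will occur, only that the stated protection against it is not there.

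**What to change.** 1. Delete the blinded-assessor claim from the quality-control paragraph, from Planned outcomes and data analysis, and from the Discussion. Describe all outcomes as open-label and participant-completed.
2. In the Discussion, replace *anonymous* with *confidential, coded*.
3. Remove blinding and anonymity from the mitigation for social desirability bias, and remove blinded assessment from the strengths. Keep self-administration and aggregate reporting.
4. Keep the analyst-blinding claim only if group and site are supplied under neutral labels, with app-use data withheld until the analysis code is locked. Otherwise withdraw it.
5. State that positive results on the Likert self-report secondary outcomes come from unblinded participants and cannot alone support a behaviour-change conclusion.

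The cost is wording plus one masked-label data extract, with no extra staff, participants or visits. The article places cleaning and analysis after follow-up ends, so on its stated timeline the masking could be set up before analysis. The stated strengths become slightly less favourable.

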## Results

Planned outcomes and data analysis

Since this is a protocol, no results are available yet. The primary outcome is ergonomic knowledge, while secondary outcomes include self-prevention behaviors and self-evaluation, measured at baseline (T0), post-training (T1), and six weeks later (T2). Analyses will follow intention-to-treat principles using repeated-measures mixed models (fixed effects: group, time, group×time), with site effects and adjustments for baseline scores and prespecified covariates (e.g., age, tenure, department/shift, prior training). Two-sided α=0.05; results will be reported as adjusted mean differences with 95% CI. Sensitivity analyses will incorporate site-clustered standard errors (SEs), a random intercept for the site if applicable, and inverse-probability-of-treatment weighting. Outcome assessors and the statistician will remain blinded to group allocation. 

Protocol Status and Timeline

Recruitment and baseline assessments are ongoing; follow-up continues through November 2025, after which data will be cleaned and analyzed. No interim results are available.

Interpretation of Change

A structured outcome framework was created to assess the effectiveness of the ARPE training module. The assessments are divided into three domains: ergonomic knowledge (the primary outcome), self-prevention behaviors (secondary outcome 1), and self-evaluation skills (secondary outcome 2). Each domain is evaluated at three key timepoints: baseline (t_0_, before the intervention), week 1 (t1, after the intervention to assess knowledge), and week 6 (t2, follow-up post-intervention). The tools used are adapted from Diego-Mas et al. [14]. All scales are scored so that higher scores reflect better outcomes. The primary endpoint is the change in ergonomic knowledge from baseline to immediate post-training (T0→T1). ARPE will be considered superior if the adjusted group-time effect (ARPE-control) is positive with a 95% CI that does not include 0 (two-sided α=0.05); persistence will be evaluated at T2. For secondary domains (self-prevention, self-evaluation), adjusted group×time effects at T1 and T2 will be regarded as improvements when the 95% CI excludes 0; these analyses are exploratory and supportive.

Baseline Characteristics

Baseline characteristics are summarized in Table 1: continuous variables are presented as mean (SD) or median (IQR), while categorical variables are shown as n. These include age, sex, ethnicity, education, job category, employment duration, shift work, MMH process details, and prior ergonomic training. To evaluate comparability between groups at t_0_, SMDs will be used instead of significance tests. Thresholds for SMD are as follows: <0.10 (negligible), 0.10-0.20 (small), and >0.20 (substantial imbalance). Variables with SMD >0.20, along with prespecified covariates such as age, tenure, department/shift, and prior training, will be adjusted for in the repeated-measures mixed models. These models will incorporate site effects and cluster-robust SEs, as detailed in the Statistical Analysis section. If baseline p-values are reported, they are purely descriptive and not used to determine equivalence.

Primary Outcome: Ergonomic Knowledge

Repeated measures (t_^0^_, t_1_, t_2_) will be analyzed using generalized estimating equations (GEE). The model includes group (ARPE vs. control), time, group×time interaction, site (fixed effect), and prespecified covariates (e.g., age, department/shift, prior training). The primary comparison is the adjusted ARPE-control difference at t_1_, obtained from the group×time term (with baseline accounted for by including t0 in the repeated-measures model); durability will be evaluated at t_2_. Results will be reported as marginal adjusted mean differences (95% CI; two-sided α=0.05) and SMDs. Within-group changes across (t_0_, t_1_, t_2_) will be derived from model-based marginal contrasts with 95% CI. Missing data will be managed under missing completely at random (MCAR)/missing at random (MAR) assumptions using GEE with robust SEs, with sensitivity analyses employing inverse-probability-weighted GEE and multiple imputation.

Secondary Outcome 1: Self-Prevention 

Self-prevention (PQ-derived domain mean; 7-point Likert scale; higher scores indicate better performance; scores are rescaled from 0 to 100) will be analyzed using GEE (identity link, Gaussian), clustering on participants with robust (sandwich) SEs and an exchangeable working correlation. The model includes group (ARPE vs. control), time (t_0_, t_1_, t_2_), group×time, site (fixed effect), and prespecified covariates (age, tenure, department/shift, prior training). Between-group change is tested via group×time with prespecified contrasts reporting marginal ARPE-control differences at t_1_ and t_2_ with 95% CI (two-sided α=0.05) and SMDs. Within-group change (t_1_-t_0_, t_2_-t_0_) will be presented using model-based marginal contrasts (descriptive). Missing data will be addressed under MCAR/MAR using GEE with robust SEs; sensitivity analyses will include inverse-probability-weighted GEE.

Secondary Outcome 2: Self-Evaluation 

Self-evaluation will be assessed using adapted RQ and SA domain means (7-point Likert scale; higher scores indicate better performance; scores are rescaled from 0 to 100). Repeated measures (t_0_, t_1_, t_2_) will be analyzed with GEE using an identity link and Gaussian family, clustering on participants with robust (sandwich) SEs and an exchangeable working correlation (Quasi-likelihood under the Independence model Criterion (for comparing GEE correlation structures) (QIC) to compare AR(1) and unstructured). The model includes group (ARPE vs. control), time, the interaction between group and time, site (fixed effect), and prespecified covariates (age, tenure, department/shift, and prior training). Between-group differences will be tested via the group×time interaction, with prespecified contrasts reporting marginal ARPE-control differences at t_1_ and t_2_ (95% CI; two-sided α=0.05; SMDs shown). Within-group changes (t_1_-t_0_, t_2_-t_0_) will be derived from model-based marginal contrasts (95% CI) and presented descriptively; inference will follow the GEE model.

Data Collection

Baseline data collection will occur during the participants' first training session, before their enrolment in the study. Both primary and secondary outcomes will be evaluated at three intervals: the baseline measurement, the end of the first week, and the conclusion of the sixth week. Participants will receive prompts to complete data collection at each point through direct reminders and easy survey submission options. During baseline collection, reminders will be provided at the initial training session, with notifications sent via WhatsApp or phone calls, as preferred by the participants. During recruitment, participants will fill out self-administered questionnaires using a Google Form. For follow-up assessments in the first and sixth weeks, the same communication channels will be used for reminders, and the Google Form will be the sole method for these evaluations. These reminders will be strategically timed to foster consistent engagement and compliance, thus facilitating accurate data collection throughout the study. This strategy ensures a thorough, flexible, and efficient monitoring of data collection over the two months.

Data Management

In the data management domain, we are committed to upholding the privacy and confidentiality of participants. To achieve this, each participant will be assigned a unique anonymous research identification number (ID). Participant names and data will be securely stored on a password-protected researcher's laptop, linked exclusively to their respective research ID for this study. Regular data backups will be executed and stored in a secure location. Upon the study's conclusion, data on the computer will be transferred to an external hard drive, and the computer data will be permanently erased. Both external hard drives and hardcopy data will be safeguarded in a locked office designated for researchers. The data will be retained for at least three years post-study completion, after which it will be systematically erased. This stringent data management protocol ensures the highest data security and participant confidentiality throughout and beyond the study period.

Data Analysis

Analyses will be conducted using IBM SPSS Statistics for Windows, Version 29.0 (IBM Corp., Armonk, New York, United States). After cleaning and verifying the data, descriptive statistics will summarize continuous variables as mean (SD) or median (IQR) and categorical variables as n (%). Baseline comparability will be assessed with SMDs (<0.10 negligible; 0.10-0.20 small; >0.20 meaningful); any baseline p-values are for descriptive purposes only.

Effectiveness analyses will use GEE with an identity link and Gaussian family, clustering on participants with robust (sandwich) SEs and an exchangeable working correlation; QIC will compare the exchangeable structure with AR(1)/unstructured structures. Models will include group (ARPE vs. control), timepoints (t_0_, t_1_, t_2_), group×time interactions, site (fixed effect), and prespecified covariates (age, job tenure, department/shift, prior ergonomic training). The primary comparison is the adjusted ARPE-control difference at t_1 _for ergonomic knowledge (0-100%); durability will be assessed at t_2_. Within-group changes (t_1_-t_0_, t_2_-t_0_) will be derived from model-based marginal contrasts and presented descriptively. Results will be shown as marginal adjusted mean differences with 95% CI (two-sided α=0.05) and SMDs. All analyses will follow intention-to-treat principles. Missing repeated measures will be addressed under MCAR/MAR assumptions via GEE with robust SEs; inverse-probability-weighted GEE and multiple imputation sensitivity analyses will also be reported. For multiple secondary domains and timepoints, multiplicity will be controlled using the Benjamini-Hochberg FDR (q=0.05) method, with both raw and FDR-adjusted p-values presented.

